# A school-based health promotion programme to increase help-seeking for substance use and mental health problems: study protocol for a randomised controlled trial

**DOI:** 10.1186/s13063-016-1510-2

**Published:** 2016-08-08

**Keywords:** Prevention, Schools, Health education, Substance misuse, Alcohol, Young people, Wellbeing, Help-seeking

## Abstract

**Background:**

Adolescence is a high-risk time for the development of mental health and substance use problems. However, fewer than one in four 16–24 year-olds with a current disorder access health services, with those experiencing a substance use disorder being the least likely to seek professional help. Research indicates that young people are keeping their problems to themselves or alternatively, turning to peers or trusted adults in their lives for help. These help-seeking preferences highlight the need to build the mental health literacy of adolescents, to ensure that they know when and how to assist themselves and their peers to access support. The MAKINGtheLINK intervention aims to introduce these skills to adolescents within a classroom environment.

**Methods/design:**

This is a cluster randomised controlled trial (RCT) with schools as clusters and individual students as participants from 22 secondary schools in Victoria, Australia. Schools will be randomly assigned to either the MAKINGtheLINK intervention group or the waitlist control group. All students will complete a self-report questionnaire at baseline, immediately post intervention and 6 and 12 months post baseline. The primary outcome to be assessed is increased help-seeking behaviour (from both formal and informal sources) for alcohol and mental health issues, measured at 12 months post baseline.

**Discussion:**

The findings from this research will provide evidence on the effectiveness of the MAKINGtheLINK intervention for teaching school students how to overcome prominent barriers associated with seeking help, as well as how to effectively support their peers. If deemed effective, the MAKINGtheLINK programme will be the first evidence-informed resource that is able to address critical gaps in the knowledge and behaviour of adolescents in relation to help-seeking. It could, therefore, be a valuable resource that could be readily implemented by classroom teachers.

**Trial registration:**

Australia and New Zealand Clinical Trials Register (ANZCTR): ACTRN12613000235707. Registered on 27 February 2013.

**Electronic supplementary material:**

The online version of this article (doi:10.1186/s13063-016-1510-2) contains supplementary material, which is available to authorized users.

## Background

### Mental health and substance use are major health issues for young people

Adolescence is a high-risk time for the development of mental health and substance use problems. Indeed, half of all lifelong mental disorders (including substance use disorders) commence by the age of 14 years, with three quarters beginning before the age of 25 [1]. In Australia, over a quarter of 16–24 year-olds meet criteria for a mental disorder in the previous 12 months, with anxiety (15.4 %), depression (6.3 %) and substance use disorders (12.7 %) being the most commonly experienced conditions [2]. Despite cross-sectional data showing an increase in non-drinking among Australian adolescents [3], harmful use of alcohol is still the most common and concerning substance use issue among this cohort. The most recent Australian Secondary Students Alcohol and Drug Survey identified that just over half of all 12–17 year-olds had consumed alcohol in the past year, and 50.7 % of this group were drinking at harmful levels by age 17 [4]. Equally concerning, in 2013, surveys showed that around one in six people aged between 12 to 18 had consumed 11 or more standard drinks on a single drinking occasion in the past 12 months [5]. Untreated mental health issues and early onset substance use often co-occur and can lead to a range of short-term harms. Ultimately, substance use can adversely impact relationships, educational and developmental milestones, as well as later mental and physical health [6].

### Young people are reluctant to seek professional help

Seeking help early is widely recognised as a generic protective factor, and promoting early and prompt treatment is critical in order to reduce the adverse impacts of mental health and substance use problems [6]. However, fewer than one in four 16–24 year-olds with a current disorder access health services, with those experiencing a substance use disorder being the least likely to seek professional help [2]. Rather than seeking professional help, research indicates that young people are keeping their problems to themselves or turning to their peers or key adults in their lives for help [7]. This is despite evidence that many parents and peers have poor mental health literacy [8], as indicated by their limited ability to recognise specific disorders, poor knowledge of how to seek mental health information, and poor knowledge of risk factors and causes, self-treatments and professional help available, as well as attitudes that do not promote recognition and appropriate help-seeking [9]. In addition, adolescents have knowledge, attitudes and beliefs about help-seeking and substance use that act as barriers to seeking professional help, and these are likely to have been established before the age of 13 [10]. Barriers identified include stigma, fears about lack of confidentiality, limited trust, lack of problem recognition, reliance on oneself, and concerns about helper characteristics. These help-seeking beliefs and preferences highlight the importance of building the mental health literacy of adolescents, including ensuring that they know when and how to assist their peers to access support.

### Schools are ideal sites for health promotion activities and strengthening gatekeeping skills

Schools are an ideal and opportunistic setting in which to reach out to young people [11], particularly in terms of facilitating future help-seeking for mental health and substance use issues. Given the low help-seeking intentions of adolescents, teachers and peers are ideally placed to play a gatekeeping role (i.e. identifying issues and intervening), by supporting and helping young people to access appropriate professional support. To be effective, gatekeepers require the skills to identify mental health issues, engage the young person and help them overcome the barriers to accessing and engaging with professional help. Additionally, there is evidence from the mental health first-aid literature that teaching people how to help their peers seek help not only improves gatekeeping skills but is an innovative approach to improving their own mental health and help-seeking attitudes [12].

### Current gaps in the curriculum and opportunities to intervene

Although some school drug and mental health education programmes have been produced that focus on youth participation and peers as educators [13, 14], to our knowledge these have generally not focussed on exploring the barriers to helping a friend, taught students the skills necessary to overcome these barriers, nor facilitated professional help-seeking. In short, they do not focus on teaching practical steps for peers to become effective gatekeepers for their friends, which in turn, would signify that they have become proficient in terms of their own help-seeking skills. To this end, we previously reported findings from a pilot help-seeking intervention study (MAKINGtheLINK), with a focus on cannabis use and mental health, delivered over two 48-minute periods to 10 year-10 classes (182 students) at a Melbourne high school, as part of their standard curriculum [15]. The delivery of the programme was found to be both acceptable and feasible within a school setting, with students reporting increased confidence and awareness of how to seek help for themselves or a friend. A second pilot, which focussed primarily on help-seeking for alcohol and mental health, was conducted over three 50-minute periods, to 16 year-8 and year-9 classes (370 students) from three Melbourne high schools, as part of their standard curriculum [16]. Students reported that the programme led to increased knowledge about alcohol, awareness of help-seeking options and confidence to seek help for an alcohol problem. While these findings are encouraging, the pilot studies included few schools, without a control arm, and did not measure any change in actual help-seeking. Before the programme can be finalised and embedded within a national school framework, the efficacy of the programme needs to be established utilising a rigorous methodological and longitudinal design.

### Aims and hypotheses

This cluster randomised trial seeks to demonstrate the efficacy of a universal, school-based intervention that focusses on reducing barriers and improving help-seeking and peer support for students who are experiencing poor mental health and/or misusing alcohol or other drugs.

The primary hypothesis to be tested is that:Participation in the intervention, compared to a waitlist control group, will lead to increased help-seeking behaviour (from both formal and informal sources) for alcohol and mental health issues at 12 months post intervention, as measured by the Actual Help Seeking Questionnaire

We will also test the following secondary hypotheses:Compared to a waitlist control group, participation in the intervention will lead to increased confidence to seek help immediately after, and 6 and 12 months post intervention as measured by the General Help Seeking QuestionnaireCompared to the control group, participation in the intervention will lead to increased confidence to assist a peer to seek help immediately after, and 6 and 12 months post intervention as measured by the General Help Seeking Questionnaire and self-reported help-seekingCompared to the control group, participation in the intervention will lead to a reduction in psychological barriers for help-seeking associated with alcohol and depression immediately after, and 6 and 12 months post baseline, as measured by the Barriers to Adolescents Seeking Help – Brief Version questionnaire

## Methods/design

### Study design

The study (see Fig. 1) is a randomised controlled trial (RCT) with schools as clusters and individual students as participants, and will follow the Standard Protocol Items: Recommendations for Interventional Trials (SPIRIT) Statement for reporting trial protocols (see Additional file 1 for checklist) [17]. All consenting participants will be assessed at four time points: baseline, 6 weeks post baseline, 6 months post baseline and 12 months post baseline. Participants from the control schools will be assessed on equivalent dates at the four time points.

**Fig. 1 Fig1:**

Schematic illustration of the research design

Twenty-two Victorian secondary schools will be recruited for the study. Schools will be randomly allocated to either receive the intervention immediately or to form a waitlist control group and receive the intervention after completion of the fourth survey. Randomisation will be stratified by the school’s Index of Community Socio-Educational Advantage (ICSEA) score, with two strata defined as <1000 (‘disadvantaged’) and 1000+ (‘advantaged’). The random allocation list will be generated using Stata statistical software, Release 12 (StataCorp, College Station, TX, USA: 2011) with random block sizes of 2 or 4 within each strata.

### Sample

Eligible participants are year-9 students (aged 14–15 years) who consent to participate in the study. Eligible schools are state, Catholic or independent schools in Victoria with between 40 and 250 year-9 students. Schools will be sent an email explaining the study and inviting participation. To be included in the sample, schools will have to be willing to support their 2013, 2014 or 2015 year-9 cohorts to participate in the health education programme offered as part of this research, as they will not know in which year they will receive the programme until randomisation and consent form collection has occurred.

### Sample size calculation

Sample size calculations accounting for cluster randomisation have been estimated using Stata 12 software (StataCorp, College Station, TX, USA: 2011). Useful background information is available from a controlled pre-post pilot study conducted in three regional high schools that were matched on socioeconomic characteristics [18]. The trial group included 171 year-11 students from mainstream classes who received a school-based intervention (Building Bridges to General Practice) that addressed adolescents’ psychological help-seeking barriers in presentations delivered by trained general practitioners (GPs) [18]. At baseline, only 1 (0.6 %) of the 171 students reported visiting a GP. At 12-week follow-up, 12 students (7.0 %) indicated receiving a consultation. Assuming the pre-test consultation rate represents the control group post measure for the proposed trial, we estimated the effect size in schools (where the intervention is implemented by trained staff as the expected difference in proportions between the control arm and the intervention arm) to be 6.4 % (pooled SD 18.8 %). Assuming 80 % successful consent and randomisation, followed by a 25 % attrition rate between baseline and follow-up, the number of students in the analysis would be 60 % of a school’s year-9 level. We anticipate that this will lead to an approximate average cluster size for analysis of 51 students per school.

It is important to note that the assumed effect size may be a conservative estimate considering the intervention’s focus on help-seeking from both formal and informal sources, rather than just GPs, who young people are reluctant to access. In other words, both the prevalence at baseline and the difference in proportions at 12-month follow-up, of students seeking help from formal and informal sources are likely to be greater than the pilot study indicates for seeking help from GPs.

For the proposed project, the intra-class correlation (ICC) is unknown, although a comparable school-based cluster randomised trial conducted by Jorm and colleagues reported an ICC of 0.05 [19]. Setting ICC (ρ) at 0.05, power (1 − β) at 80 %, and a two-sided level of significance at 5 % (*α* = 0.05), the required number of individuals per treatment arm is 476 students corresponding to a need for 10 schools per arm. The desired sample size was 1020 and this was increased to 1360 to allow for 25 % dropout by the 12-month follow-up assessment.

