A cluster randomised approach was adopted as this has the advantage of controlling for potential contamination of information between individuals in the same setting (i.e. between control and intervention students in the same school). Our previous experience with MAKINGtheLINK is that the lessons learnt in the classroom are often embraced by the school community, and as such, individual randomisation within a school setting would have created additional confounds. Including measures of school disadvantage, as well as other demographic and clinical data, provides an opportunity to explore predictors of help-seeking outcomes within particular school environments, as well as how the intervention is influenced by current mental health symptoms and past help-seeking behaviour.

A number of changes were made to the programme that built on the findings from the two pilot studies. These studies demonstrated that the programme was both highly feasible and acceptable within school settings [15], and led to an initial reduction in help-seeking barriers and increase in intentions to seek help from formal sources [16]. However, these effects were not consistently maintained at follow-up 6 weeks later, as participants’ help-seeking intentions had returned to baseline levels at this time point. In response to these findings, the programme was expanded to include the addition of a booster session 1 month after the initial intervention, given evidence that this can increase retention of knowledge and improve outcomes. The booster session provided students with a second opportunity to practice help-seeking skills using a different video scenario of a young person struggling with personal issues, as well as a poster-making activity that provided students with the opportunity to share their knowledge with other year groups. Materials from the two previous pilots were further refined, with additional mental health examples and case studies added to the programme, as well as a discussion of the mental health continuum, which increased the length of the overall intervention. Teacher training was offered to staff across the school, and a newsletter was provided to staff to ensure that they were aware of the agreed referral process within the school and were able to provide a helpful response if approached by students.

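### The 80% power applies to a GP-visit outcome with a 0.6% control rate, not to the primary outcome, and the remark that the effect size may be conservative omits that higher prevalence lowers power for a given absolute difference

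*Protocol article*

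**What the plan says.** The abstract defines the endpoint: "The primary outcome to be assessed is increased help-seeking behaviour (from both formal and informal sources) for alcohol and mental health issues". Its time point is 12 months. Aims and hypotheses and Statistical analysis both name the AHSQ as the instrument, and the analysis is logistic regression.

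The Sample size calculation section uses a different outcome. Both rates come from GP visits in the 171 students who received the intervention in a pilot study of another programme. The starting rate is given as "At baseline, only 1 (0.6 %) of the 171 students reported visiting a GP", and the later rate is 12 of 171 (7.0%) at 12 weeks. The first becomes the control rate by assumption: "Assuming the pre-test consultation rate represents the control group post measure for the proposed trial". The result is a difference of 6.4 points, a pooled SD of 18.8%, and 476 students (10 schools) per arm at 80% power. Study design sets the trial at 22 schools.

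The section then offers a reassurance: "It is important to note that the assumed effect size may be a conservative estimate". The reason given is that, for help from any source, "both the prevalence at baseline and the difference in proportions at 12-month follow-up" are likely to be greater than the GP figures. Neither is given a value.

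**The concern.** For a binary outcome the variance is p(1 − p), which climbs steeply as p moves away from zero. The SD of 18.8% is that small only because the assumed control rate is close to zero. The article expects a higher rate for the real endpoint and lists this among its reasons for comfort, but it does not revisit the SD. On its own, that change works against power for a given absolute difference. Only the other half of the argument, a larger difference, works in its favour.

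At stake is how the trial is read. The 80% figure is the only statement of what the design can detect, and the Discussion links adoption in a national school framework to the result. If the figure does not carry over to the AHSQ outcome, readers have no stated basis for judging an inconclusive primary result.

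**Working it through.** **Inputs from the article.** Two-sided alpha 5%; power 80%; control rate 0.6%; intervention rate 7.0%; difference d = 0.064; SD 0.188; 51 analysed students per school (already net of attrition); ICC 0.05; 22 schools, taken as 11 per arm.

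**Inputs that are assumptions.** Control rates of 2%, 5%, 10% and 20% for the AHSQ outcome. The article gives none, so a range is shown.

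**Step 1: reproduce the plan.**
- SD = √[(0.006 × 0.994 + 0.07 × 0.93) / 2] = 0.1885, the stated 18.8%.
- n before clustering = 2 × (1.96 + 0.8416)² × 0.188² / 0.064² = 135.5, rounded up to 136 per arm.
- Design effect = 1 + (51 − 1) × 0.05 = 3.5.
- 136 × 3.5 = 476 per arm, and 476 / 51 = 9.3, so 10 schools per arm. This matches exactly; the arithmetic is sound.
- 2 × 10 × 51 = 1020, and 1020 / 0.75 = 1360, also as stated.

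**Step 2: hold d at 6.4 points and change only the control rate.**
- Effective n per arm with 11 schools = 11 × 51 / 3.5 = 160.3.
- SD(p) = √{[p(1 − p) + (p + 0.064)(1 − p − 0.064)] / 2}.
- SE = SD × √(2 / 160.3).
- Power is taken at d / SE, once with the normal distribution and once with the noncentral t on 2 × 11 − 2 = 20 df.

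Example at 5%: SD = √[(0.0475 + 0.1010) / 2] = 0.272; SE = 0.0304; d / SE = 2.10; normal power = Φ(2.10 − 1.96) ≈ 56%.

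**Step 3: find the difference that restores 80% power (t)** at each control rate, letting the variance change with the difference.

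| Control rate | SD at 6.4 points | Power, normal | Power, t | Difference for 80% (t) | Multiple of 6.4 |
|---|---|---|---|---|---|
| 0.6% (plan) | 18.8% | 86% | 82% | 6.1 points | 1.0 |
| 2% | 22.0% | 74% | 70% | 7.6 points | 1.2 |
| 5% | 27.2% | 56% | 52% | 9.7 points | 1.5 |
| 10% | 33.7% | 40% | 37% | 11.9 points | 1.9 |
| 20% | 42.1% | 28% | 25% | 14.5 points | 2.3 |

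The 0.6% row exceeds 80% because 22 schools are planned and the calculation needs 20. With 10 schools per arm, t-based power is 78%, 65%, 48%, 34% and 23% down the same rows.

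**The case against.** The strongest reply is that the table changes one assumption and freezes the other. The article says both the prevalence and the difference will be larger, it hedges with *may*, and it applies the word conservative to the effect size, not to the power or to the 0.6% rate. If the difference grew as well, power would hold: with 11 schools per arm (normal), 10 points at a 5% control rate gives 86%, 12 points at 10% gives 84%, and 15 points at 20% gives 86%. This stands. A reader might infer that the article's remark is simply false; the documents do not show that.

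Second, the analysis is logistic, so the odds ratio is a natural scale. The planning rates imply an odds ratio of (0.07/0.93) / (0.006/0.994) ≈ 12.5, whereas the differences in the last three rows of the table correspond to about 3.3, 2.5 and 2.1. Higher prevalence therefore makes smaller relative effects detectable. This also stands, and it is why the point is confined to a given absolute difference, the scale on which the article states its effect. It does not make the 80% figure apply to the AHSQ outcome.

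Third, the control rates are assumptions. That is correct. At 2% the loss is moderate.

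Three further arguments are tempting and carry no weight:
- A rate for professional help could be built from the Background figures, but those describe 16–24 year-olds, and one is only an upper bound. The trial enrols 14–15 year-olds and asks about the past 6 months.
- The Discussion reports of the second pilot that "these effects were not consistently maintained at follow-up 6 weeks later", but the return to baseline it describes is in intentions, not behaviour, and a booster session was added in response.
- A 0.6% control rate would leave very few control-arm events, but that requires the rate to be true, whereas the present point concerns what follows if it is higher.

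**Conclusion.** The passage is wrong as written on two counts. It presents 80% power for the trial when the inputs describe a GP-visit outcome with a 0.6% control rate. It also counts an expected rise in prevalence among its grounds for comfort without saying that this rise costs power for a given absolute difference.

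The size depends on a control rate that the article does not give. For 6.4 points with 22 schools of 51 and ICC 0.05, t-based power is about 70% at a 2% control rate and falls to 25% at 20%. The reassurance holds only if the true difference grows to about 7.6 to 14.5 points over the same range, that is 1.2 to 2.3 times the planned one. No figure in the article supports such growth.

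A reader might go further and say that the trial has only 25–50% power, or can detect only very large differences. The documents do not support that as an unconditional statement: it needs both an assumed control rate of roughly 5–20% and a difference held at 6.4 points. The calculations also assume equal school sizes and the article's ICC.

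**What to change.** In the Sample size calculation section:

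1. Remove the remark about a conservative effect size, or qualify it by stating that higher prevalence raises the variance and by giving the difference needed to keep 80% power.
2. State that the 80% figure applies only at a control rate near 0.6%, as for the GP-visit outcome.
3. Restate power and minimum detectable difference for the AHSQ any-source outcome with 22 schools. Take the pooled baseline AHSQ prevalence, without splitting by arm, as the guide to the control rate, and add a short table over plausible control rates in the form shown above. With completion expected in mid-late 2016 and a 12-month follow-up, the baseline data should already be in hand.

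No extra enrolment and no change to the design or analysis is needed. The cost is some text, one table, and a stated power that will probably look less favourable.
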